### Sequence generation and allocation concealment

2.9

Two sets of random sequences will be generated for the 2 research institutions using the statistical program SAS (SAS institute Inc, Cary, NC) by an independent statistician. The block size will not be known to the investigators so as not to predict the random sequence. All participants will have equal chances of being selected for either the Mokhuri treatment group or the control group. Sealed opaque envelopes with the assigned results for each participant will be used for allocation concealment. The investigators at each of the study institutions will open a random assignment envelope and assign the participant to an intervention group in the consecutive order of the patients’ serial numbers.

### Outcomes

2.10

The validated English version for the Mayo Clinic and the Korean version for the Mokhuri hospital will be used for all the outcome assessments. Outcome assessors will be blinded to the allocation results.

The primary outcome will be VAS scores from 0 to 100 for low back pain. The degree of pain will be evaluated on a 100 mm straight line, where the left edge of the straight line will indicate “0: no symptoms,” and the right edge will indicate “100: the most severe pain.” The participant will indicate the average level of lumbar pain experienced for the past week.

The secondary outcomes will include VAS scores from 0 to 100 for leg pain, EQ-5D scores, Oswestry disability index (ODI) scores, Roland–Morris Disability Questionnaire (RMDQ) scores, Zurich Claudication Questionnaire (ZCQ) scores, walking duration and distance without leg pain, a 5-minute treadmill test, the ratio between the actual duration of participation and the originally scheduled duration in each group, the presence of any additional spondylolisthesis treatments, the types of concomitant treatments during the follow-up period, and adverse events (AEs).

For assessing leg pain, a VAS score from 0 to 100 for leg pain will be assessed. The participant will indicate the average level of leg pain experienced for the past week. The EQ-5D is a common assessment tool for measuring health-related quality of life. It contains 5 dimensions including mobility, self-care, usual activities, pain (discomfort), and anxiety (depression). In this study, we will use the EQ-5D-3L, which has 3 levels of severity for each dimension.^[10,11]^ The ODI consists of 10 topics concerning pain, lifting, ability of self-care, ability to walk, sit, stand and travel, sexual function, social life, and sleep quality and is intended to assess disability and quality of life related to low back pain. ODI scores range from 0 (no disability) to 100 (maximum disability possible).^[12,13]^ The RMDQ is a tool that is widely used for evaluating the functional conditions of patients with low back pain. It contains 24 statements regarding the patient's perceptions about pain and disability, such as physical activity, sleep, psychosocial, and pain frequency. RMDQ scores range from 0 (no disability) to 24 (maximal disability possible).^[14,15]^ The ZCQ is an instrument for assessing pain and symptoms related to spinal stenosis. It consists of 3 domains with 18 questions assessing the symptom severity over the last month, physical functioning over the last month on a specific day, and the patient's satisfaction with current treatment. The results are recorded as a percentage of the possible maximum score, and higher scores represent worse conditions.^[16]^ The walking duration and distance without leg pain and a treadmill test will be used to assess the physical function of the patients. Patients will be asked to walk a distance of 25 m on a round track at their preferred speed, and the distance will be measured when they are no longer able to walk due to pain in the lower limb or lumbar region. For the treadmill test, the participants will walk on the level treadmill at a speed of 1.5 miles per hour, and the time until they start to feel pain in their legs will be measured.^[17]^ The presence of any additional treatments for spondylolisthesis and the types of treatments will be assessed during the follow-up period. Because the treatments in each of the groups will end, patients will be allowed to use additional treatments for spondylolisthesis if they wish to. During this period, participants will be asked whether they used other additional treatments for symptoms related to spinal spondylolisthesis and what types of treatments they used. The ratio between the actual duration of participation and the originally scheduled duration in each group will be assessed as well. Participants whose VAS scores from 0 to 100 for back pain and leg pain decrease below 1 at every weekly evaluation will stop the treatment immediately, according to the early termination rule of this study. The number of patients who stop the scheduled treatments early and the number of those who finish all the scheduled treatments will be assessed in each group, and the differences in the ratio between groups will be assessed. AEs will be assessed during each visit. Participants will be asked to report AEs voluntarily, and researchers will observe participants’ conditions on a regular basis. For each reported AE, the symptoms, signs, starting date, duration, severity, and causal relationship will be assessed by researchers.

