According to the results of our previous observational study involving Mokhuri nonsurgical integrative treatments performed on patients diagnosed with Meyerding grade 2 lumbar spinal spondylolisthesis, considerable clinical improvement was observed after nonsurgical integrative treatments; the average walking distance without pain increased from 55 to 165 m, while the intensity of pain experienced when walking was reduced by 80% compared with the baseline assessment.^[7]^ In another previous retrospective audit study, on a numeric rating scale from 0 to 10, 44 spondylolisthesis patients reported a reduction in numeric rating scale scores from 7.1 to 3.1, and walking distance without pain increased from 193 to 568 m after treatment.^[8]^ These observational studies provide clues for the potential benefit of nonsurgical integrative treatments and suggest that these treatments might be effective for pain relief and functional restoration in patients with symptomatic lumbar spinal spondylolisthesis. However, observation studies cannot provide clinical evidence, so these new therapeutic options should be evaluated through rigorous, high-powered clinical trials.

The objective of this study is to assess the effectiveness and the safety of a 5-week Mokhuri treatment program compared with conventional nonsurgical treatments for symptomatic lumbar spondylolisthesis.

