### Inclusion and exclusion criteria

2.3

Individuals who meet all the following criteria will be included as appropriate participants in the clinical trial:(1)Those aged from 19 to 78 years;(2)Those with a diagnosis of degenerative lumbar spinal spondylolisthesis or who have low back pain, lower limb radiating pain, or leg discomfort when standing or walking with a severity of at least 5 on a visual analogue scale (VAS) of 0 to 100 for each symptom;(3)Those suffering from neurologic claudication or radicular pain for at least 1 year;(4)Those with neurogenic claudication within 5 minutes of walking on a treadmill at a speed of 1.5 miles per hour;(5)Those who have not received an epidural injection within the past month;(6)Those who have not undergone lumbar surgery;(7)Those who have confirmed spondylolisthesis on lumbar spine AP, lateral, nd both oblique views;(8)Those who weigh 250 lbs (113.398 kg) or less;(9)Those whose height is 2.1 m (6.890 ft) or shorter; and(10)Those who agreeing to participate in this clinical trial after receiving a thorough explanation of the purposes and characteristics of the trial and who are willing to sign the written informed consent form.

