
### Participant time schedule

2.11

At the screening visit, participants will be given detailed explanations of the objectives and contents of this clinical trial and will receive the written agreement form. During this visit, a 5-minute treadmill test, lumbar physical and radiological examinations, ankle-brachial index assessment (or Doppler ultrasonography of lower limbs if necessary), bone mineral densitometer assessment, and inclusion criteria assessment will be conducted. If the participant can be enrolled in the study, random assignment of the participant will take place at the following visit. Before the treatments begin, the VAS scores for low back pain and for leg pain, EQ-5D scores, ODI scores, RMDQ scores, ZCQ scores, walking duration and distance free of leg pain, and a treadmill test will be assessed. After that, participants will undergo 10 treatments over 5 weeks. After treatment, evaluations will be performed immediately (7 weeks) and at 18 weeks, 30 weeks, 54 weeks (1-year follow-up), and 102 weeks (2-year follow-up). AEs will be assessed at each visit (Table 1).

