### Statistical analysis

2.13

Statistical analysis will be performed based on an intention-to-treat analysis for the assessment of effectiveness outcomes and a per-protocol analysis for the assessment of safety. The missing values will be substituted with the most recently observed value (the last observation carried forward method). For the demographic information, continuous data will be presented as the mean and SD, and categorical data will be reported with a frequency table. The 2-sample *t* test (or Wilcoxon rank-sum test) will be used for the analysis of continuous variables after evaluating the data distribution. For categorical data, the chi-square test (or Fisher exact test) will be used. Outcome variables including VAS scores for lumbar pain and leg pain, EQ-5D scores, ODI scores, RMDQ scores, ZCQ scores, walking duration and distance without leg pain, and the treadmill test will be summarized with means and SDs. For statistical analysis of continuous outcomes, changes in the scores before and after treatments will be regarded as dependent variables, with the baseline scores and research institutions as covariates and the groups as fixed factors, to perform the analysis of covariance. To verify the trends for each visit in the 2 groups, repeated measures analysis of variance will be performed. For categorical outcome data, the chi-square test (or Fisher exact test) will be used.

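### The track outcome is named for pain-free walking but measured at inability to walk; the treadmill time, a lesser point, needs a stated maximum and a label to match

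*Protocol article*

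**What the plan says.** **Track walk.** Section 2.10 (Outcomes) lists among the secondary outcomes "walking duration and distance without leg pain, a 5-minute treadmill test". The Abstract, the participant schedule (2.11) and the statistical section (2.13) use the same or an equivalent name. Section 2.10 then says how the track walk is scored: "the distance will be measured when they are no longer able to walk due to pain in the lower limb or lumbar region". It describes no timing of that walk.

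**Treadmill.** Section 2.10 says "the participants will walk on the level treadmill at a speed of 1.5 miles per hour" and that "the time until they start to feel pain in their legs will be measured". The Abstract and the outcome list call it a 5-minute test. So does the screening visit in 2.11 ("During this visit, a 5-minute treadmill test, lumbar physical and radiological examinations"), while the same section lists the pre-treatment assessment simply as a treadmill test. Inclusion criterion 4 in section 2.3 reads "Those with neurogenic claudication within 5 minutes of walking on a treadmill at a speed of 1.5 miles per hour". No section gives a stopping time for the outcome test or says what is recorded for someone who finishes without pain.

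**Analysis.** Section 2.13 states that "walking duration and distance without leg pain, and the treadmill test will be summarized with means and SDs". Continuous outcomes are analysed by ANCOVA of the change score, with baseline score and institution as covariates.

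**The concern.** Pain-free distance and maximum tolerated distance are different quantities. A participant may feel leg pain early and walk on for a long way, or may stop for back pain without any leg pain. The track outcome carries the name of the first quantity and the measurement rule of the second. If sites follow the rule, the published pain-free distance will not be one, and onset that was not noted during the walk cannot be recovered later. Nor would a reader be able to set the result beside the pain-free distances that motivate the trial; for one of these the Introduction reports that "walking distance without pain increased from 193 to 568 m after treatment".

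The treadmill raises a smaller question of interpretation. Entry requires symptoms within 5 minutes at the test speed, so improvement moves people towards the limit that the test's name implies. If the test does stop there, the mean is not the mean of full pain-free walking time, and section 2.13 does not say so.

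**Working it through.** The plan gives no numerical target for the walking outcomes, so there is no figure of its own to reproduce.

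**1. Track walk: name against measurement (no arithmetic needed)**

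| | Outcome as named | Outcome as measured (2.10) |
|---|---|---|
| Event that ends the measurement | Leg pain begins | Participant can no longer walk |
| Site of pain | Leg | Lower limb or lumbar region |
| Quantities | Duration and distance | Distance only |

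The two differ on every row. The treadmill sentence in the same section uses onset of leg pain, so the plan has an onset definition available and does not apply it to the track.

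**2. Treadmill: what a 5-minute limit would record**

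Inputs from the protocol: speed 1.5 mph, limit 5 minutes (from the test's name), and pain-free distances in the Introduction of 55 to 165 m (observational study) and 193 to 568 m (retrospective audit).

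- Speed: 1.5 × 1609.344 / 3600 = 0.6706 m/s.
- Distance at the limit: 0.6706 × 300 = 201.2 m.
- Cited post-treatment means against the limit: 165 / 201.2 = 0.82 and 568 / 201.2 = 2.82.

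Share of participants at the limit. Assumptions not in the protocol: log-normal distances, CV 0.6 to 1.0, and cited distances that carry over to the treadmill at 1.5 mph. With σ² = ln(1 + CV²) and μ = ln(mean) − σ²/2, the share is Φ((μ − ln 201.2)/σ).

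- CV 0.6: σ = 0.5545. Mean 165 m gives μ = 4.952 and Φ(−0.635) = 26%. Mean 568 m gives μ = 6.188 and Φ(1.595) = 94%.
- CV 1.0: σ = 0.8326. Mean 165 m gives μ = 4.759 and Φ(−0.654) = 26%. Mean 568 m gives μ = 5.996 and Φ(0.831) = 80%.

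Effect on the mean difference. The full difference is the difference in mean distance divided by 0.6706. With c = 201.2 m and m the mean distance, the mean restricted to the limit is [m·Φ((ln c − μ − σ²)/σ) + c·(1 − Φ((ln c − μ)/σ))] / 0.6706. The protocol gives no follow-up mean for controls, so a range is shown.

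| Treated mean (cited) vs control mean (assumed) | Full difference | Restricted to 300 s, CV 0.6 | Restricted to 300 s, CV 1.0 |
|---|---|---|---|
| 165 vs 100 m | 97 s | 66 s | 52 s |
| 568 vs 193 m | 559 s | 67 s | 81 s |
| 568 vs 380 m | 280 s | 11 s | 22 s |

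The restricted difference is smaller in every row, but by how much depends on the control mean assumed.

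**3. Would a censored analysis do better?** Simulated trials with log-normal times gave similar power for ANCOVA of the limited time and for Cox regression censored at 5 minutes: 0.57–0.60 against 0.57–0.61 at 568 vs 380 m, and 0.92–1.00 against 0.90–1.00 at 165 vs 100 m. With no true difference (both means 380 m, 55 per arm, baseline–follow-up correlation 0.5, no institution term), ANCOVA rejected in 0.048 to 0.059 of trials. The level of power moves with these settings; the closeness of the two methods is what matters here.

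**The case against.** The strongest reply concerns the treadmill. A reader might infer that the time is definitely capped, that the planned ANCOVA is therefore invalid, and that a real effect would almost vanish. The documents do not support this.

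- The cap is inferred from the test's name and criterion 4. The sentence defining the measurement sets no stopping time, and how pain-free finishers are scored may be in the full protocol, which is not shown.
- The most striking shrinkage, 280 s to 11–22 s, needs an assumed control mean of 380 m. It also leaves out the cited study whose post-treatment mean, 165 m, lies below the limit.
- The mean of time limited at 5 minutes is a legitimate quantity, a restricted mean. It understates a difference only against a full pain-free time that a 5-minute test cannot observe.
- A Cox or log-rank analysis uses the same limited data, so it recovers neither the lost difference nor any useful power.

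All of this stands, and it reduces the treadmill issue to one of labelling and reporting.

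On the track walk, it can be said that the text is compressed (whether 25 m is a lap or the whole walk is unclear), that the plan proposes no formal comparison with the earlier studies, and that the outcome is secondary. These points limit the consequence. They do not remove the contradiction: the sentence states a measurement rule, and that rule does not yield the named outcome.

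**Conclusion.** The track part holds on the text alone and rests on no assumption. The outcome is named for duration and distance free of leg pain, the rule records maximum tolerated distance ended by leg or back pain, and no duration is described.

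The treadmill part holds as a minor, conditional point. If the test stops at 5 minutes, the mean in section 2.13 is a mean pain-free time restricted to 300 s. Under the log-normal assumption, the treated share at the limit runs from about 26% (mean 165 m) to 80–94% (mean 568 m). The mean difference then understates the difference in full pain-free time by an amount that the protocol's figures do not fix. It does not follow that the planned test is invalid or that another model would rescue it.

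Both are secondary outcomes. The primary back-pain analysis and the sample size are untouched.

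**What to change.** **Track walk.** In section 2.10, have the assessor note distance and elapsed time at first leg pain and use these for the named outcome. Let the participant walk on as now, and report distance at inability to walk as a separate outcome called maximum walking distance. The cost is one extra recorded time point in a test already planned. It has to be in place before data are collected.

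**Treadmill.** State the maximum duration of the outcome test and make it agree with the test's name. If it is 5 minutes, say that a participant who finishes without pain is recorded at 300 s, label the result as pain-free time up to 5 minutes, and report by group the proportion completing 5 minutes without leg pain. The planned ANCOVA can remain under that label. A time-to-event analysis censored at 5 minutes is an acceptable alternative, but should not be presented as recovering power or the unobserved difference. This changes wording and adds one summary, with no further procedure.

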
### Participant time schedule

2.11

At the screening visit, participants will be given detailed explanations of the objectives and contents of this clinical trial and will receive the written agreement form. During this visit, a 5-minute treadmill test, lumbar physical and radiological examinations, ankle-brachial index assessment (or Doppler ultrasonography of lower limbs if necessary), bone mineral densitometer assessment, and inclusion criteria assessment will be conducted. If the participant can be enrolled in the study, random assignment of the participant will take place at the following visit. Before the treatments begin, the VAS scores for low back pain and for leg pain, EQ-5D scores, ODI scores, RMDQ scores, ZCQ scores, walking duration and distance free of leg pain, and a treadmill test will be assessed. After that, participants will undergo 10 treatments over 5 weeks. After treatment, evaluations will be performed immediately (7 weeks) and at 18 weeks, 30 weeks, 54 weeks (1-year follow-up), and 102 weeks (2-year follow-up). AEs will be assessed at each visit (Table 1).

**Table 1 T1:**
[figure not shown]
Participant schedule.

### Sample size

2.12

To calculate the sample size, a retrospective study performed on 44 patients with lumbar spinal spondylolisthesis^[8]^ and the previous clinical trial data that assessed physical therapy for hospitalized patients in a similar study setting^[18]^ were used. To determine a meaningful difference between groups, a minimal clinically important difference of 2.5 points on the numeric rating scale of 0 to 10 was used.^[19]^ The standard deviation (SD) was 4.65 from the abovementioned previous studies. For the sample size calculation, the significance level (α) was 0.05, and the power (1–β) was 0.80. The following formula was used for the calculation. Assuming a drop-out rate of 10%, 61 participants will be needed in each study group, yielding a total of 122 participants needed for this study. 
[figure not shown]

In terms of the total 122 participants in the study, 108 participants will be recruited at the Mokhuri Oriental Medicine Hospital and 14 participants at the Mayo Clinic.

### Statistical analysis

2.13

Statistical analysis will be performed based on an intention-to-treat analysis for the assessment of effectiveness outcomes and a per-protocol analysis for the assessment of safety. The missing values will be substituted with the most recently observed value (the last observation carried forward method). For the demographic information, continuous data will be presented as the mean and SD, and categorical data will be reported with a frequency table. The 2-sample *t* test (or Wilcoxon rank-sum test) will be used for the analysis of continuous variables after evaluating the data distribution. For categorical data, the chi-square test (or Fisher exact test) will be used. Outcome variables including VAS scores for lumbar pain and leg pain, EQ-5D scores, ODI scores, RMDQ scores, ZCQ scores, walking duration and distance without leg pain, and the treadmill test will be summarized with means and SDs. For statistical analysis of continuous outcomes, changes in the scores before and after treatments will be regarded as dependent variables, with the baseline scores and research institutions as covariates and the groups as fixed factors, to perform the analysis of covariance. To verify the trends for each visit in the 2 groups, repeated measures analysis of variance will be performed. For categorical outcome data, the chi-square test (or Fisher exact test) will be used.

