**Objectives::**

The objective of this study is to assess the effectiveness and safety of a 5-week Mokhuri treatment program compared with conventional nonsurgical treatments for symptomatic lumbar spondylolisthesis.

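### The per-protocol set is the only population stated for safety, so who enters the adverse-event comparison can depend on harm itself and can differ by arm

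*Protocol article*

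**What the plan says.** Section 2.13 (Statistical analysis) names two analysis populations in one sentence: "an intention-to-treat analysis for the assessment of effectiveness outcomes" and "a per-protocol analysis for the assessment of safety". The article does not define the per-protocol set, and it names no all-treated or as-treated set.

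Safety is part of the stated aim. The Introduction gives the objective as "to assess the effectiveness and the safety of a 5-week Mokhuri treatment program compared with conventional nonsurgical treatments", and the Abstract and section 2.1 agree. AEs are listed among the secondary outcomes in section 2.10, which adds that "AEs will be assessed during each visit"; section 2.11 repeats this.

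Section 2.10 also foresees early stopping, counted by arm: "The number of patients who stop the scheduled treatments early and the number of those who finish all the scheduled treatments will be assessed". The stopping rule it describes is triggered by low pain scores, not by harm. Section 2.12 allows for 10% drop-out, with 61 participants per group.

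**The concern.** A safety analysis should include everyone exposed to the treatment. A per-protocol set, as the term is normally used, keeps those who completed or adhered. A participant who stops a drug because of a side effect, forgoes an injection after a bad reaction, or gives up manual therapy because it hurts may leave that set because of the event the analysis is meant to count.

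The arms also differ in what adherence requires. Under sections 2.4 to 2.6, one arm attends 10 sessions of acupuncture, Chuna and consultation. The other takes daily drugs, has one or two epidural injections and attends 10 physical therapy sessions. The routes out of the set differ, so the exclusions can differ too, and randomisation no longer protects the comparison.

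At stake is the between-group safety comparison, which is a named objective. The last-observation-carried-forward rule in section 2.13 does not help, because it cannot restore someone who is outside the analysis set.

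**Working it through.** **The plan's own figure.** The finding does not depend on the sample size, but the illustration borrows from it. Inputs from section 2.12 are a difference of 2.5, an SD of 4.65, and "the significance level (α) was 0.05, and the power (1–β) was 0.80". A two-sided test is assumed.

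- n per arm = 2 × (1.960 + 0.842)² × 4.65² / 2.5² = 54.3, rounded up to 55.
- With 10% drop-out: 54.3 / 0.9 = 60.3, rounded up to 61. The stated 61 is reproduced.
- 10% of 61 is 6.1, so about 6 per arm are allowed for, leaving 55.

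**One arm.** Assumptions: 8 of 61 have the AE of interest (8/61 = 13.1%), and 6 are excluded from the per-protocol set. Let k be the number of those 6 who had the AE. The reported rate is (8 − k) / 55.

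| k | Reported rate |
|---|---|
| 0 | 8/55 = 14.5% |
| 1 | 7/55 = 12.7% |
| 2 | 6/55 = 10.9% |
| 4 | 4/55 = 7.3% |

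The rate is understated when the excluded participants have a higher AE risk than the arm as a whole, and overstated when they have a lower one. With these counts the balance lies at 6 × 8/61 = 0.8 of the excluded having the AE. One or more gives understatement; none gives slight overstatement.

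**Two arms.** Let p be the true AE risk and f the share of participants with an AE who leave the set. Suppose for simplicity that no one else leaves. The reported risk is p(1 − f) / (1 − pf). The risks below are assumed.

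| True risks | Share lost (f) | Reported risks | Difference, true → reported |
|---|---|---|---|
| 20% v 10% | 25% v 0 | 15.8% v 10.0% | 10 → 5.8 points |
| 20% v 10% | 50% v 0 | 11.1% v 10.0% | 10 → 1.1 points |
| 20% v 10% | 50% v 50% | 11.1% v 5.3% | 10 → 5.8 points |
| 20% v 20% | 50% v 0 | 11.1% v 20.0% | 0 → −8.9 points |

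For example, 0.20 × 0.5 / (1 − 0.20 × 0.5) = 0.10 / 0.90 = 11.1%. This case removes 0.20 × 0.5 × 61 = 6.1 participants from the arm, the same number as the drop-out allowance. A real difference can nearly vanish, and a difference can appear where there is none.

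**The case against.** The strongest objection is that the per-protocol set is undefined. Membership might turn on completion, compliance or receipt of the allocated treatment, and such definitions are often left to a full protocol or analysis plan that is not shown. If the authors meant an as-treated grouping, much of the concern disappears. This stands as a limit: exclusion of harmed participants follows from the usual meaning of the term, not from a written rule. It does not rescue the clause. The choice of population is stated rather than omitted, and an analysis plan that followed it in its ordinary sense would carry the problem forward.

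Three stronger readings are tempting, and the article does not support them.

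- *AE rates will be understated in each arm.* The sign depends on who is excluded, as the k = 0 row shows. The only early-stopping rule described is for low pain scores. If the set required all 10 sessions, those participants could be excluded as well, for reasons unrelated to harm.
- *Serious events in people who leave the protocol will go unrecorded.* AEs are assessed at each visit, and recording is not limited to a per-protocol set. Section 2.13 restricts the analysis only.
- *The AE rate will be roughly halved.* That comes from assuming that 4 of 6 excluded participants had the AE. The 10% is a drop-out allowance in a trial followed to week 102, not a per-protocol exclusion rate for a 5-week treatment. Late loss need not be a deviation, and a participant can deviate without dropping out.

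It is also fair to say that AEs are a secondary outcome, that the trial is not sized on safety, and that the primary effectiveness analysis is untouched.

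**Conclusion.** The concern holds in conditional form. The article fixes a per-protocol set as its only safety population, which is the wrong choice for that purpose. Recorded AEs in excluded participants may fall outside the between-group comparison, AE rates can be understated, and a safety difference can be hidden or created.

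The size and sign cannot be computed from the article. Under the assumed 8 of 61 with an AE and 6 excluded, the reported rate runs from 14.5% down to 7.3% against a true 13.1% as 0 to 4 of those excluded had the AE. The conclusion rests on the usual meaning of per-protocol and on harm being one reason for stopping or deviating. It does not rest on any particular exclusion rate. Because safety is a named objective and the clause is explicit, it should be corrected before the data are analysed.

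**What to change.** Replace the safety clause in section 2.13 with:

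*Safety is analysed in all randomised participants who received at least one trial treatment session, drug dose or injection, grouped by treatment actually received, counting every AE including those leading to stopping.*

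Keep any per-protocol analysis as supplementary only.

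The cost is one sentence. No new data are needed, because AEs are already collected at every visit. Reported AE rates may become less favourable.
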